## Methods

### Aims

The primary aim of this randomized clinical trial is to investigate the effectiveness of an online BC intervention based on both SDT and TTM in increasing PA and reducing sedentary behavior in adults with asthma. Secondary aims are (I) to observe the impact of this intervention on asthma control, functional capacity, quality of life, sleep quality, and symptoms of anxiety and depression; (II) to verify whether the BC intervention improves the satisfaction of BPNs, self-determination and autonomous forms of motivation for PA; and (III) to investigate if the effects of the BC intervention will be maintained in the medium term (6 months after the end of intervention).

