### Participants

Participants will be recruited through the referral of pulmonologists from outpatient clinics of Londrina and São Paulo, Brazil. Study publicization will be performed on social media too; however, patients who come in contact must be undergoing medical follow-up. This study will include people aged from 18 to 60 years, with a physician-based diagnosis of moderate to severe asthma (confirmed by checking the history of variable respiratory symptoms and treatment [15]) who underwent drug treatment for at least 6 months; with clinical stability for at least 1 month (without hospitalizations, emergency care use or medication changes). Additionally, absence of cardiovascular and/or osteoneuromuscular diseases that could interfere/hinder the performance of tests and physical activity, absence of lung diseases other than asthma, preserved cognitive function [16], non-smokers or ex-smokers with <10 pack-years, report being physically inactive in accordance with current physical activity guidelines [17], and people who are able to make video calls through any platform and/or free app available. The exclusion criteria comprise the presence of any physical limitation that compromises mobility and hinders PA performance during the participation period.

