### Sample size calculation

The sample calculation was based on a previous study with adults with asthma in which two groups performed a 12-week intervention to increase physical activity, and the number of steps/day obtained in both groups (control and experimental) were normally distributed with the following values after the intervention: 6248±2030 and 8853±3320 steps/day, respectively [11]. Therefore, for the present study, a total sample of 38 people will be needed to reject the null hypothesis, with a power of 0.8 and a value of *P*<0.05. However, considering a 20% drop-out rate [13] throughout the study, the final sample size will be 46 people (23 in each group).

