### Statistical analysis

Statistical analysis will be performed after post-intervention and follow-up assessments using the software SPSS Statistics V22.0 (IBM, USA). Data distribution will be analyzed using the Shapiro-Wilk test. Variables will be presented as mean (SD), median [interquartile range 25–75%] according to data distribution. Categorical variables will be presented as absolute and relative frequency. The magnitude of statistical estimates will be presented using 95% CI. The results will be analyzed according to the intention-to-treat principle, as recommended by the CONSORT statement [40]. Per-protocol analysis might be performed to contrast results. Mixed model ANOVA will be used to identify the effect of the protocol to promote physical activity and reduce sedentary behavior. The repeated measures factor will be “time” (pre- and post-intervention evaluation) and the independent measures factor will be the “group” (control group or intervention group). To compare the proportion of patients that achieved the minimal clinical important difference in ACQ and AQLQ (0.5 points for both) [22, 41] between groups, the chi-square test will be used. Pearson or Spearman correlation coefficients will be used to verify the relationship between the changes in PA and changes in asthma control or quality of life. Values of *P* <0.05 will be considered statistically significant.

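### For ACQ and AQLQ the plan ties only a chi-square on a 0.5-point cut to the group comparison, and leaves unclear whether the scores are also compared on the continuous scale

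*Protocol article*

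**What the plan says.** Three statements in the protocol article's Statistical analysis section bear on ACQ and AQLQ.

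- The responder comparison: "To compare the proportion of patients that achieved the minimal clinical important difference in ACQ and AQLQ (0.5 points for both" points), and "between groups, the chi-square test will be used".
- The mixed ANOVA, with time (pre and post) and group as factors: "Mixed model ANOVA will be used to identify the effect of the protocol to promote physical activity and reduce sedentary behavior". No outcomes are listed beyond this phrase.
- A correlation for the "relationship between the changes in PA and changes in asthma control or quality of life". This uses the continuous changes but does not compare the groups.

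The Aims section puts both scales under secondary aim I: "to observe the impact of this intervention on asthma control, functional capacity, quality of life, sleep quality, and symptoms of anxiety and depression". The Participants section requires moderate to severe asthma "with clinical stability for at least 1 month (without hospitalizations, emergency care use or medication changes") and sets no minimum ACQ or AQLQ impairment at entry. The sample size rests on steps per day alone: "a total sample of 38 people will be needed to reject the null hypothesis, with a power of 0.8".

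**The concern.** A responder cut treats a change of 0.4 as no change and a change of 2.0 as equal to 0.5. In a trial of this size that loss matters. If the chi-square is the planned group comparison, the trial could report a non-significant test of two proportions as its result for asthma control and quality of life, when the same data would have given a more precise mean difference with a confidence interval.

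The cut also has a floor. ACQ starts at 0 (no impairment), so a patient who enters below 0.5 cannot fall by 0.5 and is a non-responder whatever the treatment does. The same applies to AQLQ within 0.5 of its best score. Nothing in eligibility keeps such patients out, and the intention-to-treat analysis keeps them in the denominator.

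A reader of the article cannot tell which analysis of these scales was planned as the main one. That leaves room to choose after the data are seen.

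**Working it through.** **Evaluable size.** From the Sample size calculation section: 6248 (SD 2030) and 8853 (SD 3320) steps per day. Pooled SD = sqrt((2030² + 3320²)/2) = 2752. Standardised difference = 2605/2752 = 0.947. A two-sided t-test at 0.05 with 80% power needs 18.5 per arm, so 19 per arm or 38 in total (power 0.81). This reproduces the plan's 38. The 46 randomised follow from 38 × 1.2 = 45.6. No power figure is given for ACQ or AQLQ, so there is none to reproduce.

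**Assumptions.** The documents give no SD, correlation or baseline mean for ACQ or AQLQ. I assume SD 1.0 at each visit, pre-post correlation 0.6, a true between-group difference of 0.5, no mean change in controls, and a two-sided test at 0.05.

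**Formulas, ignoring the floor.**

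- SD of change = 1.0 × sqrt(2 × (1 − 0.6)) = 0.894.
- ANCOVA residual SD = 1.0 × sqrt(1 − 0.6²) = 0.80.
- Responder probability, control = 1 − Φ(0.5/0.894) = 0.288; intervention = 1 − Φ(0) = 0.50.
- With two time points, the time-by-group interaction in the mixed ANOVA is the t-test on change.

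| Per arm | Chi-square (exact enumeration) | Change score / ANOVA | ANCOVA |
|---|---|---|---|
| 19 | 0.29 | 0.39 | 0.47 |
| 23 | 0.32 | 0.46 | 0.55 |

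**Simulation with scores limited to 0-6**, 19 per arm, true effect 0.5 (uncorrected Pearson chi-square):

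| Assumed baseline mean ACQ | Chi-square | Change score / ANOVA | ANCOVA |
|---|---|---|---|
| 1.5 | 25% | 35% | 44% |
| 1.0 | 20% | 33% | 41% |

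The gap between chi-square and ANCOVA has two parts. At baseline mean 1.5 it is 44 − 25 = 19 points: 35 − 25 = 10 from dichotomising and 44 − 35 = 9 from baseline adjustment. At baseline mean 1.0 it is 41 − 20 = 21 points: 33 − 20 = 13 and 41 − 33 = 8.

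**Sensitivity of the dichotomising loss.** I varied the SD of change from 0.6 to 1.0, the true difference from 0.3 to 0.7, and the control change between 0 and 0.2. The chi-square needs 1.58 to 1.81 times as many patients as the change-score test for the same power. Absolute power depends heavily on the assumed SD; the relative loss hardly does.

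**Gain from baseline adjustment.** Variance ratio of ANCOVA to change score = 0.80²/0.894² = 0.64/0.80 = 0.80, which is (1 + 0.6)/2. At this correlation ANCOVA does the same work with about 20% fewer patients than the ANOVA.

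**Floor.** Under the assumed normal baseline, about 16% (mean 1.5) or 31% (mean 1.0) start below ACQ 0.5. These shares come from the assumption, not from the documents. To see the effect on power, take 23 per arm, SD of change 0.8, difference 0.5 in the rest, and let the share with no room to improve rise from 0% to 40%. Chi-square power falls from 0.37 to 0.20, and change-score power falls from 0.55 to 0.24. Both tests are diluted; the chi-square stays the weaker at every share.

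**Small expected counts.** At 19 per arm, an expected count fell below 5 in up to about 15% of simulated trials; at 23 per arm, in about 3% at most.

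**The case against.** The strongest objection is that the ANOVA may already cover ACQ and AQLQ. A reader might infer from the ANOVA sentence that this model is reserved for physical activity and sedentary behavior, so that the clinical scales get a chi-square and nothing else. The documents do not support that. The Abstract and the Design and setting section use almost the same words to describe the intervention, so the sentence can equally mean the effect of that intervention on every continuous outcome. On the narrow reading, functional capacity, sleep, anxiety and depression, psychological needs and motivation would have no group test at all. On the wide reading, the chi-square is an added responder analysis. This objection stands against calling the chi-square the sole planned test. It does not remove the ambiguity, and it does not touch the gain from adjusting for baseline.

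It can also be said that a condensed article need not list a model for each secondary outcome. That is fair, and silence alone would be no finding. Here, though, the article does specify a group test for these two scales, and it is the less efficient one.

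A further objection is that the choice of test is not the main reason a 0.5-point benefit could be missed. This stands: even ANCOVA has under 50% power at 19 per arm under the assumptions used. The floor also weakens a continuous test, and sparse cells are uncommon if all 23 per arm are analysed.

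**Conclusion.** The point holds as a matter of clarity and efficiency. One between-group test is tied by name to ACQ and AQLQ, it dichotomises at 0.5, and the text does not settle whether the scores are also compared by the ANOVA.

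- If the chi-square is the main comparison, moving to ANCOVA raises power for a true 0.5-point effect from about 20-25% to 41-44%.
- If the ANOVA is, the rise is from about 33-35% to 41-44%.

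Both rest on assumed SD 1.0, correlation 0.6, baseline mean 1.0 to 1.5 and 19 per arm. The share of patients below ACQ 0.5 at entry is unknown: stability is defined by absence of hospitalisation, emergency care and medication change, not by a low ACQ.

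A reader might conclude that the chi-square would make the trial miss an effect that it would otherwise detect. The figures do not support that. These are secondary outcomes with no claimed power, and under these assumptions a 0.5-point effect would more likely than not be missed at 19 per arm with any of the three tests. The case for the change is a more precise estimate with a usable interval, at no cost in patients.

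**What to change.** In the Statistical analysis section, state that ACQ and AQLQ are compared between groups as continuous scores by ANCOVA adjusted for the baseline score. Report the adjusted mean difference with its 95% CI and read it against 0.5 points. Say which outcomes the mixed ANOVA covers.

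Keep the 0.5-point responder proportions as a supportive analysis in all randomised patients. Report a risk difference, and use an exact test if an expected count falls below 5. Giving the number in each arm with no room to improve at baseline would help readers interpret the proportions.

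The cost is a sentence or two of analysis wording, best fixed before the data are analysed. It needs no extra patients, visits or measurements, because both scores are already planned outcomes.

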## Discussion

BC intervention has been considered vital to optimize and maintain benefits from intervention in chronic care [42]. The intervention described in this study is unprecedented. It was carefully developed to joint most characteristics and techniques of both TTM and SDT [2, 4]. Additionally, it was included objective feedback to the patients (activity monitor) with weekly goals adapted from a previous study [19]. Furthermore, this intervention will be online, but with direct weekly contact with the therapist. Online interventions might improve participant attendance and has the potential to be largely offered elsewhere, including confinement conditions as experienced around the world with the COVID-19 pandemic. Studies in different populations showed that online intervention to increase PA is effective, easy to perform, and has low implementation costs. We hypothesize that this intervention will achieve positive results in the PA, sedentary behavior, asthma management, and global health of this population; therefore, supporting its use in clinical practice.

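### The correlation of change in physical activity with change in asthma control or quality of life should account for arm, because the trial expects the intervention to move both

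*Protocol article*

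**What the plan says.** The protocol article, Statistical analysis, plans a Pearson or Spearman analysis, worded as follows: "correlation coefficients will be used to verify the relationship between the changes in PA and changes in asthma control or quality of life". The section ends with a general significance rule: "Values of *P* <0.05 will be considered statistically significant".

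The correlation sentence does not mention group. Two neighbouring sentences do. The mixed model ANOVA is set up so that "the independent measures factor will be the “group” (control group or intervention group"), and the chi-square test of responder proportions in ACQ and AQLQ is explicitly a comparison between groups.

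The Discussion states the expected direction: "We hypothesize that this intervention will achieve positive results in the PA, sedentary behavior, asthma management, and global health of this population". The Sample size calculation gives the only figures for the size of the PA effect: "6248±2030 and 8853±3320 steps/day, respectively" for control and experimental groups after the intervention in a previous study.

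**The concern.** Across two randomised arms, a simple correlation of two changes has two sources. One is the relation among patients within an arm: whether those who became more active than others in their own arm also gained more asthma control or quality of life. The other is the gap between arms. If the intervention raises PA and separately improves ACQ or AQLQ, intervention patients tend to sit at the favourable end of both variables and control patients at the other end. A correlation then appears even if the two changes are unrelated within each arm.

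The second source vanishes only if the intervention fails to move one of the two variables, and the trial hypothesises the opposite. The coefficient therefore becomes harder to interpret the better the intervention works.

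The components that could produce this are those given only to the intervention group: the weekly therapist contact and the activity monitor with its goals (Behavior change intervention). The educational program goes to both arms and cannot create a between-arm component. At stake is whether a significant coefficient says anything about patients who became more active, or only restates that the intervention affected both outcomes.

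**Working it through.** **Inputs from the document.** Steps/day after intervention: control 6248 (SD 2030), experimental 8853 (SD 3320); power 0.8; 38 evaluable; 46 randomised, 23 per group (all from Sample size calculation). Significance threshold P<0.05 (Statistical analysis).

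**Assumptions.** The test is two-sided, as sidedness is not stated. The PA effect d1 comes from post-intervention SDs, because change-score SDs are not given. The standardised effect d2 on ACQ or AQLQ change is not in the document and is varied from 0 to 0.8. Changes are normal with equal variance in the two arms, which are of equal size.

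**1. The plan's own figure.**
- Pooled SD = √((2030² + 3320²)/2) = 2751.7.
- Difference = 8853 − 6248 = 2605, so d1 = 2605/2751.7 = 0.947.
- A two-sample t-test with two-sided α 0.05 and power 0.80 needs 18.53, hence 19 per arm, or 38 in total. This reproduces the stated requirement, "a total sample of 38 people will be needed to reject the null hypothesis, with a power of 0.8".

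**2. Correlation induced by pooling.** With within-arm SD 1 and within-arm correlation 0, the pooled covariance is d1·d2/4 and the pooled variances are 1 + d1²/4 and 1 + d2²/4. Hence

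r = (d1·d2/4) / √[(1 + d1²/4)(1 + d2²/4)].

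With d1 = 0.947, d1²/4 = 0.224:
- d2 = 0.2: 0.0473/√(1.224 × 1.010) = 0.04
- d2 = 0.3: 0.0710/√(1.224 × 1.0225) = 0.06
- d2 = 0.5: 0.118/√(1.224 × 1.0625) = 0.10
- d2 = 0.8: 0.189/√(1.224 × 1.16) = 0.16

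These are absolute values. For ACQ the induced sign is negative, because a lower score is better.

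**3. Chance of P<0.05 when the within-arm correlation is zero.** There were 40,000 simulated trials per setting. The pooled Pearson test uses N−2 degrees of freedom. The arm-adjusted test removes arm means and uses N−3.

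| Assumed d2 | Induced \|r\| | Pooled, N=38 | Pooled, N=46 | Arm-adjusted, N=38 | Arm-adjusted, N=46 |
|---|---|---|---|---|---|
| 0 | 0 | 5.1% | 5.0% | 5.0% | 5.0% |
| 0.2 | 0.04 | 5.7% | 5.8% | 5.1% | 4.8% |
| 0.3 | 0.06 | 6.6% | 7.0% | 4.7% | 5.0% |
| 0.5 | 0.10 | 9.9% | 10.2% | 5.2% | 4.8% |
| 0.8 | 0.16 | 16.2% | 18.7% | 5.1% | 4.9% |

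Pooled Spearman is nearly identical (for example 9.8% at d2 = 0.5 and 16.2% at d2 = 0.8, N=38), so the rank option gives no protection. The N=46 column requires that nobody drops out, whereas the plan allows for 20%.

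**The case against.** The strongest reply is that pooling is inferred from silence. The sentence does not say that all patients enter one coefficient. Separate coefficients in each arm would also fit it, and a condensed article may leave that detail to a fuller plan. This stands in part: pooling cannot be asserted as fact. But the method named is a plain bivariate coefficient, and the adjacent analyses name group while this one does not. One coefficient over all patients is therefore the most natural reading, and specifying the adjusted form settles the matter either way.

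Second, the rejection rates are false-positive rates only if the target is the within-arm relation. When the intervention moves both variables, the pooled correlation really is non-zero, and rejecting zero is correct for that quantity. This also stands. The issue is which relation the coefficient describes; the test itself is not invalid.

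Third, a reader might infer that the trial plans to claim that becoming more active is what improves asthma control. The document does not support that. It speaks of a relationship, and no stated aim is a mediation question. The secondary aim "to observe the impact of this intervention on asthma control, functional capacity, quality of life, sleep quality" concerns the effect of the intervention, not this coefficient.

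Fourth, adjusting for arm sets aside the variation in PA that the intervention itself produced, so it answers a different question from the pooled coefficient. That is true. It is why the reported result should state which relation it describes.

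**Conclusion.** The point holds as a modest improvement to a supportive analysis. It does not demonstrate an error. Followed literally on all patients, the planned coefficient mixes arm effects with the within-arm relation under the trial's own hypothesis. At 38 analysed, with d1 = 0.95 and an assumed d2 between 0.2 and 0.8, this induces |r| of about 0.04 to 0.16 and raises the chance of P<0.05 from 5% to about 6% to 16% when there is no within-arm relation. At the low end the effect is negligible, and with d2 = 0 it is absent.

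The size rests on d2, which is wholly assumed, and on post-intervention SDs standing in for change-score SDs. Larger assumed effects would give higher rates, but the document offers no figures to support them. A reader might go further and conclude that the plan certainly ignores arm, or that any significant correlation would be spurious. Neither follows: within-arm coefficients are not excluded, and a real within-arm relation may exist. The primary comparison of PA and sedentary behavior is unaffected.

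**What to change.** Replace the simple coefficient with a partial correlation (Pearson or rank) between change in PA and change in ACQ or AQLQ, controlling for group. Alternatively, regress change in ACQ or AQLQ on change in PA with group as a covariate. Report the coefficient with its 95% CI and show the within-arm values descriptively. Describe the result as an association: changes within an arm can still share other causes, so adjustment for group does not establish mediation.

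The cost is one sentence in the plan and one degree of freedom. No new data are needed.

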### Ethics

This study complies with the Declaration of Helsinki, was approved by Research Ethics Committee (5.005.112), and has been registered on ClinicalTrials.gov (NCT05241223). All results will be disseminated via article publication. Any changes made in this protocol will be reported in the research results article. All patients will sign the informed consent before participating and will receive one of its two copies. Data will be collected in paper forms and then entered in spreadsheets which will be double-checked. Participants will be assigned an identification code for all documentation; their personal data will be handled only by the research group and will not be disclosed. This study is not funded, therefore, there are no financial conflicts of interest.

## Discussion

BC intervention has been considered vital to optimize and maintain benefits from intervention in chronic care [42]. The intervention described in this study is unprecedented. It was carefully developed to joint most characteristics and techniques of both TTM and SDT [2, 4]. Additionally, it was included objective feedback to the patients (activity monitor) with weekly goals adapted from a previous study [19]. Furthermore, this intervention will be online, but with direct weekly contact with the therapist. Online interventions might improve participant attendance and has the potential to be largely offered elsewhere, including confinement conditions as experienced around the world with the COVID-19 pandemic. Studies in different populations showed that online intervention to increase PA is effective, easy to perform, and has low implementation costs. We hypothesize that this intervention will achieve positive results in the PA, sedentary behavior, asthma management, and global health of this population; therefore, supporting its use in clinical practice.

